### Study measurements and outcomes

3.4

This trial has comprehensive baseline and final measurements of all trial outcomes (Table 1). Additionally, at baseline we will collect demographic details about the child (age, gender, ethnicity, and socio-economic status of their immediate family), their medical history (focusing on CP diagnosis, the severity of neurological impairments, and any other prevalent medical conditions including comorbid disorders) and their primary caregiver (relationship to the child, educational background, and involvement in the child's daily care).

**Table 1 tbl1:** Overview of instruments and timepoints.

Questionnaire/Activity	Study start	During study					
	Visit 1 (0 month)	Follow up 1 month (±5 days)	Follow up 2 months (±5 days)	Follow up 3 months (±5 days)	Follow up 4 months (±5 days)	Follow up 5 months (±5 days)	Visit 2 (6 months ± 15 days)
Information for parents	✓						
Signed Informed consent	✓						
Demographic questionnaire	✓						
Collected Health record data	✓						✓
Psychodiagnostic test DP-3	✓						✓
Nutrition questionnaire by Speech therapist	✓						✓
EDACS or mini EDACS	✓						✓
Pedi-EAT_	✓						✓
3-day Food diary	✓						✓
Nutrition Questionnaire about feeding problems and food preferences	✓						✓
Quality of life questionnaire	✓						✓
Anthropometry	✓						✓
Biochemical tests	✓						✓
Follow up interview after Visit 1 (e-mail)				✓			
Follow up interview after Visit 1 (GSM)		✓	✓		✓	✓	

Importantly, child assessments will be conducted by a multidisciplinary team consisting of nutritionists, speech therapists, psychologists, pediatric gastroenterologists. A nutritionist will use the findings from the assessment and collaborate with the team in developing the individualized nutritional plans for children in the intervention arm (see below).

During intake, further assessment of the inclusion and exclusion criteria will occur, alongside evaluation for the presence of comorbid disorders. Family and Child Characteristics will be collected, including:1Demographic Details: Age, gender, ethnicity, and socio-economic status of the child and their immediate family2Medical Profile**:** A detailed recording of the child's medical history, focusing on CP diagnosis, the severity of neurological impairments, and any other prevalent medical conditions including comorbid disorders.3Acute medical conditions Profile: Additional data on the number type and frequency of acute medical issues in the last 6 months will be collected4Caregiver's Profile: Information on the primary caregiver's relationship to the child, their educational background, and their involvement in the child's daily care.5Developmental assessment will be based on the Developmental Profile-3 test (DP-3) ([9], which evaluates development from birth to age 12 across five functional domains: Physical Development, Adaptive Behavior, Social-Emotional Development, Cognitive Development, and Communication. The DP-3 is conducted in the form of an interview with the child's parents or caregivers, and the instrument is administered by certified psychologists. The developmental assessment scale DP-3 is standardized for Bulgaria, and the obtained quantitative results allow for a comparative analysis with the results of a normative sample by age and gender. Additionally, it enables reporting differences in each of the functional areas of development before and after the application of a given intervention.6Quality of Life and Needs Assessment:●Needs Assessment**:** Structured interviews and surveys to explore the effects of the child's neurological challenges on family dynamics and support systems.●Quality of Life Measure: Employing established and validated tools, such as the Beach Center Family Quality of Life Scale, this assessment method systematically gauges families' perceptions across critical dimensions including Family Interaction, Parenting, Emotional Well-being, Physical/Material Well-being, and Disability-Related Support.7Dysphagia Evaluation:●Eating Abilities Analysis: Conducted by a speech therapist using the Pediatric Evaluation of Disability Inventory - Eating Module (PEDI-EAT) to assess speech, oral motor function, communication skills, and feeding and swallowing abilities.●Direct Feeding Assessment: In-depth evaluation through clinical examinations, caregiver interviews, and mealtime observations using the Eating and Drinking Ability Classification System (EDACS) and mini-EDACS.●Direct Swallowing Examination**:** Clinical evaluations and oral motor assessments to ensure safety during eating and drinking.8Nutritional Status Assessment: Conducted by a nutritionist, including measurements of height, weight, skinfold thickness, and mid-upper arm circumference, with results plotted against WHO standards and CP-specific growth charts. Dietary intake will be assessed using a 3-day food diary, a Food Frequency Questionnaire (FFQ), and evaluations of food and texture preferences, as well as gastrointestinal issues such as constipation, dysphagia, and gastroesophageal reflux.

### Randomization

3.5

We aim to enroll 100 children in the study. After successful recruitment, participants will be randomized in a 1:1 ratio into one of two groups: the intervention group, which will receive a comprehensive nutritional intervention, and the control group, which will receive standard care (Fig. 1).

**Fig. 1 fig1:**
[figure not shown]
Flowchart of study process.

The randomization process will employ a computer-generated sequence, with stratification based on gender and Gross Motor Function Classification System (GMFCS) levels. For the latter, participants will be divided into two groups: those classified on GMFCS levels 1 to 3 and those classified on GMFCS levels 4 and 5 Baranek et al., [10]. Stratification will ensure a balanced representation of motor impairment variation across the intervention and control group.

### Intervention

3.6

*Nutritional Intervention Arm* The baseline comprehensive nutritional assessment will lay the groundwork for a tailored nutrition plan informed by the assessment outcomes and guided by the national nutrition recommendations for children in Bulgaria [11], registered dietitians will develop personalized dietary recommendations for each child. These recommendations will be designed to address the unique dietary needs and challenges of each participant, taking into careful consideration their individual food preferences, sensitivities, and essential nutritional requirements. Adjustments in diet may include modifications to the texture, taste, and presentation of food, aiming to enhance food acceptance and meet nutritional goals. In certain cases, the introduction of dietary supplements, ranging from enteral formulas to fortified foods or more comprehensive measures like enteral nutrition, is recommended in accordance with ESPGHAN guidelines [12].

The support and monitoring of this intervention are carried out by qualified nutritionists or dieticians. This involves a structured follow-up mechanism that includes monthly phone check-ins and a comprehensive email consultation at the end of the third month. These interactions aim to address any nutrition-related concerns, assess adherence to the dietary recommendations, and make necessary adjustments. The adherence to the nutritional plan is further evaluated during a 6-month visit, primarily through the improvement in dietary intake as documented in a three-day food diary.

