### Standard care comparison

3.7

Participants assigned to the *Standard Care Arm* receive the conventional care typically provided to children with neurological impairments in their respective daycare or residential centers. This standard care encompasses a range of services, including regular health check-ups, therapeutic services, and educational support, aimed at addressing the general needs of children with CP.

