#### Evaluating nutritional progress

3.8.1

The study will assess the nutritional status of participants using key physical measurements, including Body Mass Index for Age Z-score (BMIAZ) when it is possible to obtain a reliable height or length measurement, Weight for Age Z-score (WAZ), Height for Age Z-score (HAZ) or Knee height for Age Z-score (if feasible), Triceps and subscapular Skinfold Thickness for Age Z-score (SFTAZ), and Mid-Upper Arm Circumference for Age Z-score (MUACAZ). Z-scores will be calculated based on WHO growth charts or CDC-charts for skin folds. Weight will be compared with CP-specific growth charts. The transformation in nutritional status is further delineated by alterations in energy intake, captured through detailed analysis of a prospective 3-day food diary. Complementing these measurements, biochemical assessments provide insights into the iron status (ferritin and Hb values), 25-OH-vitamin D levels, and vitamin B12 concentrations, offering a comprehensive view of the nutritional intervention's impact.

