## Planned analyses

4

The outcomes of the intervention will be assessed using both Intention-to-Treat (ITT) and Per-Protocol (PP) approaches. In the ITT approach, analyses include all study participants who were randomized to either of the study arms. In the PP approach, the analyses are restricted to participants who adhere to the protocol. We will not perform any imputation for missing data. Typically, the ITT method is favored for trials aiming to demonstrate superiority or non-equivalence (such as our study), PP approach is more suitable for trials assessing equivalence or non-inferiority Ahn et al., [15]. Nonetheless, it is advisable to execute both methods of analysis and compare their outcomes to identify any notable discrepancies. Employing both the ITT and PP strategies offers a fuller understanding of the effects of the treatment and enhances the credibility of the trial findings. In the case of the ITT analysis, we will focus on Weight for age Z-score (WAZ) (based on WHO standards 2006–2007) [16]. As WAZ is a standardized score for an individual given population norms, we anticipate the intervention to produce change at the tails of the distribution (for children outside the normal range) rather than the center (children in the normal range). This suggests that, in the intervention group, the baseline WAZpre variable may have a cubic relationship with the outcome WAZpost variable (Fig. 2).

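### The only stated 6-month adherence measure is improvement in diary intake, an outcome of the trial that can select only in the intervention arm; if it defines the per-protocol set, that analysis is biased by selection

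*Protocol article*

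**What the plan says.** **Adherence (section 3.6).** The monthly calls and the month-3 email serve, among other things, to "assess adherence to the dietary recommendations, and make necessary adjustments". No rule is given for turning these contacts into adherent or not adherent. Then "The adherence to the nutritional plan is further evaluated during a 6-month visit", and this is done "primarily through the improvement in dietary intake as documented in a three-day food diary". No threshold or direction of improvement is given.

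**The same diary as an outcome (section 3.8.1 and Table 1).** Nutritional status is "further delineated by alterations in energy intake, captured through detailed analysis of a prospective 3-day food diary". Table 1 schedules the "3-day Food diary" at Visit 1 and Visit 2 only.

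**Controls (section 3.7).** They "receive the conventional care typically provided to children with neurological impairments". They have no dietary plan, and no adherence criterion is stated for them.

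**The PP set (section 4).** In this approach "the analyses are restricted to participants who adhere to the protocol". The article runs PP beside ITT, intends to look for differences between the two, and regards having both as making the findings more credible. It says that ITT is the preferred approach for a superiority trial such as this one.

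**The concern.** A PP set is meant to show the effect among children treated as planned. That requires adherence to describe what was delivered and taken up, not how the child responded. Improved intake is what the plan is meant to cause, and it lies on the path to WAZ, the focus of the ITT analysis. A child whose family followed every recommendation but whose recorded intake did not rise would count as non-adherent. A child whose intake rose for other reasons would count as adherent.

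The criterion can also act in one arm only. Intervention children would be kept because of a favourable post-randomisation change, while controls with the same unfavourable change would stay in. For energy intake the comparison would be circular: children kept because intake improved would have their intake compared with that of controls not selected on it. For WAZ the bias depends on how closely intake change and weight change are related.

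At stake is the reading of PP against ITT. A larger PP effect would look like efficacy among adherent families, yet could appear with no effect at all.

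**Working it through.** **1. How the sections fit together.** Section 4 needs a definition of adherence. The only 6-month measure is the diary measure in section 3.6. The same instrument at the same visit supplies the intake outcome in section 3.8.1. Section 3.7 gives controls nothing to which the measure could apply.

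**2. Yardstick from the plan.** Section 4.1 states that 100 children allow detection of f² = 0.075 with power 0.8. For two equal arms, f² = d²/4, so d = 2 × √0.075 = 0.55 residual SD. The readable text does not state alpha. At an assumed two-sided 0.05, with noncentrality √(0.075 × 100) = 2.74 and 97 degrees of freedom, power is 0.774 rather than 0.80. That is a separate matter; 0.55 SD serves here only as a scale.

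**3. Size of the selection bias with no treatment effect.** Let r be the correlation between intake change and the WAZ residual from model (1), and p the share of the intervention arm kept, taking the largest improvements. The documents give neither, so both are assumed. The expected false benefit in residual SD is

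bias = r × φ(z) / p, with z the standard normal quantile at 1 − p.

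- r = 0.3, p = 0.5: z = 0, φ = 0.399, bias = 0.3 × 0.399 / 0.5 = 0.239.
- r = 0.3, p = 0.7: z = −0.524, φ = 0.348, bias = 0.3 × 0.348 / 0.7 = 0.149.

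Against 0.55 SD these are 0.239/0.55 = 43% and 0.149/0.55 = 27%.

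**4. Simulation.** 4,000 null trials per setting, 50 children per arm, model (1), two-sided 5% test, all controls kept. Entries are false benefit in residual SD, with the false-positive rate in brackets.

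| r | 70% kept | 50% kept | 40% kept |
|---|---|---|---|
| 0 | 0.00 (5%) | 0.00 (5%) | 0.00 (5%) |
| 0.2 | 0.09 (7%) | 0.16 (10%) | 0.19 (11%) |
| 0.3 | 0.15 (10%) | 0.24 (16%) | 0.28 (19%) |
| 0.5 | 0.24 (19%) | 0.41 (38%) | 0.48 (44%) |

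When the same intake rule is applied to both arms, bias is about 0 and the false-positive rate about 5% throughout. The one-sided selection is therefore the cause.

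**5. If improvement depends on direction.** Fig. 2 of the article expects underweight and overweight children to move in opposite directions. Suppose improvement means higher intake below WAZ 0 and lower intake above it, and let q be the share of children below 0. The two parts then partly cancel in the main effect, leaving roughly (2q − 1) times the bias in step 3. At r = 0.3 the simulated main effects are:

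| Share below WAZ 0 | 70% kept | 50% kept |
|---|---|---|
| 50% | 0.00 (5%) | 0.00 (4%) |
| 75% | 0.07 (6%) | 0.12 (8%) |
| 90% | 0.11 (8%) | 0.19 (12%) |

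For example, 0.239 × (2 × 0.75 − 1) = 0.12. What leaves the main effect goes partly into the Treatment by Baseline term, whose false-positive rate rises to as much as about 12%. Section 4 would read that interaction as an intervention effect.

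**The case against.** The strongest reply is that the article never says the diary measure defines the PP set. Section 3.6 describes monitoring, section 4 does not refer back to it, and a condensed article may leave the PP definition to a fuller plan. This stands in part: the link is an inference. It remains the natural one, since no other operational criterion is given, and the stated measure is badly chosen if it is used.

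Second, the calls and email also assess adherence, so the diary is not the whole assessment. This is correct, but no rule is attached to those contacts.

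Third, a reader might infer that PP sets responders against every control. The documents do not support that. Selection would be on intake, not on WAZ, and controls can leave the set for other reasons, such as an eligibility breach or a missed Visit 2. What holds is that this criterion removes no control.

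Fourth, dietary intake in section 3.6 is a wider term than energy intake in section 3.8.1, and intake is not among the four secondary analysis areas listed in section 4.1. The overlap is of instrument and visit rather than of identical variables. Selection on a post-randomisation response remains.

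Fifth, the largest figures in the first table need r = 0.5, a large share of the arm discarded and one direction of improvement for every child. None of these comes from the documents. Step 5 shows that direction-specific improvement shrinks the main-effect bias, to about zero if children are split evenly around WAZ 0. It does not remove the problem, because the interaction term then carries part of it.

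**Conclusion.** The point holds conditionally. If the measure in section 3.6 decides who enters the PP set, PP is biased under no treatment effect whenever intake change correlates with residual WAZ change. A fair illustration is 0.15 to 0.24 residual SD at r = 0.3 with 70% to 50% kept and one direction of improvement. The bias in the main effect is smaller, and partly shifted to the Treatment by Baseline term, if improvement is direction-specific. The correlation, the share kept and the direction are all assumptions; only a correlation of zero removes the problem altogether.

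Two stronger readings should be avoided. One is that PP favours the intervention by construction, whatever the circumstances: with direction-specific improvement the main effect can be unbiased. The other is that the trial's main result is compromised: the ITT analysis of WAZ does not use the adherence measure and is unaffected. The consequence is limited to PP, and to the PP versus ITT comparison that section 4 intends to interpret. The point merits correction, but not as a threat to the primary inference.

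**What to change.** - Define adherence for the PP set before group identities are revealed, using process measures from the four calls and the month-3 email already in Table 1: contacts completed, and caregiver-reported implementation of the recommendations.
- Apply common criteria to both arms: eligibility met, no outside dietary programme, Visit 2 within its window.
- Keep 3-day-diary change as an outcome only, and reword section 3.6 to match. If a fuller plan already defines the PP set otherwise, align section 3.6 with it.
- State that PP is supportive and may still be subject to selection, since process adherence also applies to one arm and may be related to prognosis.

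The cost is wording, plus structured recording of adherence at existing contacts. The downside is reliance on caregiver report. No change to design, sample size or visits is needed.

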### Standard care comparison

3.7

Participants assigned to the *Standard Care Arm* receive the conventional care typically provided to children with neurological impairments in their respective daycare or residential centers. This standard care encompasses a range of services, including regular health check-ups, therapeutic services, and educational support, aimed at addressing the general needs of children with CP.

### Outcomes

3.8

#### Evaluating nutritional progress

3.8.1

The study will assess the nutritional status of participants using key physical measurements, including Body Mass Index for Age Z-score (BMIAZ) when it is possible to obtain a reliable height or length measurement, Weight for Age Z-score (WAZ), Height for Age Z-score (HAZ) or Knee height for Age Z-score (if feasible), Triceps and subscapular Skinfold Thickness for Age Z-score (SFTAZ), and Mid-Upper Arm Circumference for Age Z-score (MUACAZ). Z-scores will be calculated based on WHO growth charts or CDC-charts for skin folds. Weight will be compared with CP-specific growth charts. The transformation in nutritional status is further delineated by alterations in energy intake, captured through detailed analysis of a prospective 3-day food diary. Complementing these measurements, biochemical assessments provide insights into the iron status (ferritin and Hb values), 25-OH-vitamin D levels, and vitamin B12 concentrations, offering a comprehensive view of the nutritional intervention's impact.

#### Health outcome metrics

3.8.2

Within a six-month framework, the study assesses health outcomes through several lenses:●The number and duration of days a child remains bedridden, offering insights into the intervention's impact on physical health.●The frequency of emergency medical visits and incidents of infections, including related hospitalizations, which serve as indicators of health stability and resilience.●Observations on days when the child's usual activities are hindered due to health issues, as well as instances where the child's health status influences family activities, revealing the broader implications of improved nutritional care.

Signs of malnutrition in CP were widespread, showing a direct link between inadequate nutrition and higher demands on healthcare services, including more frequent hospital stays and doctor appointments. This nutritional deficit also led to reduced engagement in everyday activities for both the child and their parent [13,14].

#### Child development and behavioral dynamics

3.8.3

The study employs the Developmental Profile 3 (DP-3) to observe changes in scores across developmental and behavioral domains. This tool enables a nuanced understanding of how nutritional interventions may influence cognitive, physical, social, and emotional development milestones.

#### Quality of life and social well-being

3.8.4

Quality of life changes and the dynamics within the social sphere are meticulously evaluated using validated instruments like the Pediatric Quality of Life Inventory (PedsQ) and the Family Impact Scale. These assessments aim to uncover the physical, emotional, social, and educational shifts experienced by the child and their family, painting a holistic picture of the intervention's effects. Furthermore, structured interviews and surveys delve into the nuances of how the child's neurological challenges and the dietary interventions interplay with family dynamics, support systems, and overall well-being.

### Assessment and participant timeline

3.9

Progress of the nutritional intervention will be monitored through monthly phone calls and a mail assessment at the third month. Assessments will occur at study entry and six months later, involving demographic and clinical interviews plus questionnaires to evaluate intervention outcomes. This schedule ensures ongoing intervention monitoring and detailed effectiveness data, detailed in Table 1 with validated standard clinical care instruments.

## Planned analyses

4

The outcomes of the intervention will be assessed using both Intention-to-Treat (ITT) and Per-Protocol (PP) approaches. In the ITT approach, analyses include all study participants who were randomized to either of the study arms. In the PP approach, the analyses are restricted to participants who adhere to the protocol. We will not perform any imputation for missing data. Typically, the ITT method is favored for trials aiming to demonstrate superiority or non-equivalence (such as our study), PP approach is more suitable for trials assessing equivalence or non-inferiority Ahn et al., [15]. Nonetheless, it is advisable to execute both methods of analysis and compare their outcomes to identify any notable discrepancies. Employing both the ITT and PP strategies offers a fuller understanding of the effects of the treatment and enhances the credibility of the trial findings. In the case of the ITT analysis, we will focus on Weight for age Z-score (WAZ) (based on WHO standards 2006–2007) [16]. As WAZ is a standardized score for an individual given population norms, we anticipate the intervention to produce change at the tails of the distribution (for children outside the normal range) rather than the center (children in the normal range). This suggests that, in the intervention group, the baseline WAZpre variable may have a cubic relationship with the outcome WAZpost variable (Fig. 2).

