**Fig. 3 fig3:**
[figure not shown]
Required sample size expecting small-to-medium effect of the intervention.

We decided to aim for a total sample of 100 participants, which will allow us to detect effects as small as f2 = 0.075 with power of 0.8. Importantly, this sample size also allows us to have reasonable confidence in detecting small-to-medium effects (e.g., f2 = 0.1) assuming a drop out rate as large as 30 % (i.e., final n = 70), which is important for per-protocol analyses.

Secondary analyses will explore nutrition's impact on health and wellbeing in children with CP, focusing on four key areas:1.Anthropometric Measures: Beyond the primary measure of Weight for Age Z-score (WAZ), we will use BMI, skin fold thickness, and mid-upper arm circumference, using age-standardized z scores, to assess the robustness of our conclusions about the effectiveness of the intervention across anthropometric indicators of nutritional status.2.Biochemical Indicators: Analyzing Vitamin D and iron levels to identify changes in nutritional deficiencies between intervention and control groups.3.Healthcare Utilization: We'll assess health indexes such as bedridden days, emergency visits, infections, hospitalizations, and impact on regular activities and family life, comparing improvements between the intervention and control groups.4.Behavior and Quality of Life: Investigating changes in child behavioral functioning and family quality of life to determine if the intervention group shows greater improvements compared to the control group.

These analyses will deepen our understanding of the nutritional intervention's broader impacts on children with CP and their families.

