## Discussion

8

This study protocol outlines a rigorous approach to evaluating the efficacy of a multidisciplinary individualized nutritional intervention for children with CP. The study would play a pivotal role in shaping future nutritional guidelines and therapeutic strategies in the management of CP.

CP is a complex condition that poses significant nutritional challenges, often leading to malnutrition and poorer health outcomes for these children da Silva et al., [20], [14]. Despite the urgency of the problem, there is a paucity of high-quality research investigating the effects of nutritional interventions in this population [21]. Our study, based on a robust randomized control design, aims to fill this critical research gap and generate much-needed evidence on this important issue.

We hypothesize that our multidisciplinary individualized nutritional intervention will result in improved growth and a decrease in the number of bedridden days, and better overall quality of life for children with CP. These outcomes are based on the understanding that better nutritional status can enhance physical health, improve functional abilities, reduce complications, and promote overall well-being.

The use of an ITT analysis approach in our study will ensure a realistic estimate of the effect of the intervention by accounting for non-compliance and protocol deviations that often occur in real-world settings. This is significant as it enhances the generalizability of our findings.

The success of this study is not only determined by the efficacy of the intervention but also by its acceptability and feasibility for the families involved. It will be essential to take into account the views and experiences of participating families, as their commitment and involvement are integral to the successful implementation of the intervention.

However, it's important to recognize potential limitations. While our study focuses on a single-center, which ensures a uniform approach to intervention implementation and data collection, it might limit the generalizability of our findings. In future, multi-center studies could be valuable for encompassing a wider variety of settings and populations.

Despite the complexities associated with this condition and the potential challenges in implementing the intervention, the study is expected to yield valuable insights that can significantly influence the care and treatment strategies for children with CP.

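### The analysis called intention-to-treat excludes every child without a six-month weight, because imputation is ruled out and no other post-baseline weight is planned

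*Protocol article*

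**What the plan says.** Section 4 (Planned analyses) defines the ITT set: "In the ITT approach, analyses include all study participants who were randomized to either of the study arms". It contrasts this with a per-protocol set limited to adherent participants, and then rules on missing values: "We will not perform any imputation for missing data". WAZ is named as the focus of the ITT analysis. Equations (1) and (2) both have WAZpost, the six-month value, as the dependent variable.

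Section 3.9 fixes when outcomes are taken: "Assessments will occur at study entry and six months later". Table 1 in section 3.4 agrees. Anthropometry is ticked at Visit 1 and Visit 2 only, and months 1 to 5 hold telephone or e-mail interviews.

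On numbers, section 3.5 says "participants will be randomized in a 1:1 ratio into one of two groups", and section 4.1 says "We decided to aim for a total sample of 100 participants". Section 4.1 also claims reasonable confidence of detecting f2 = 0.1 if drop-out is as high as 30%, leaving 70 children, and calls this important for the per-protocol analyses.

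The Discussion (section 8) relies on the approach: "The use of an ITT analysis approach in our study will ensure a realistic estimate of the effect of the intervention". That sentence goes on to give the reason, which is that ITT takes account of non-compliance and departures from the protocol.

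**The concern.** The population statement and the missing-data rule conflict for any child who has no Visit 2 weight. The regression needs WAZpost, nothing may be imputed, and no intermediate weight exists for a repeated-measures likelihood model to use. The child is simply dropped.

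Two things are at stake. First, the result would be reported as applying to all randomised children when it applies to those who came back. Secondly, loss may differ between arms in amount or in reason. Section 3.6 describes dietary changes, monthly calls and an e-mail consultation for intervention families, and section 3.7 describes none of these for standard care. If loss depends on how the child's weight is developing, the treatment contrast is biased.

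Section 4 proposes to compare ITT with per-protocol results as a check on credibility. That comparison cannot show this bias, because a child with no WAZpost is absent from both sets.

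**Working it through.** **Does the model keep a child without Visit 2?**

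| Element | Source | Consequence for a child with no Visit 2 weight |
|---|---|---|
| ITT includes everyone randomised | Section 4 | Should be analysed |
| WAZpost is the dependent variable | Section 4, equations (1) and (2) | Needs an observed or imputed value |
| Weight measured at months 0 and 6 only | Table 1, section 3.9 | No interim value to model |
| No imputation | Section 4 | Excluded |

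The first row and the last are compatible only if no child misses Visit 2. Section 4.1 does not assume that.

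**How many children?** The protocol's own ceiling gives 100 × (1 − 0.30) = 70, which matches its stated final n. A drop-out without a Visit 2 weight is lost to the ITT regression as well as to the per-protocol one. The reverse does not hold: a child who abandons the diet but is weighed at Visit 2 stays in ITT. The two sets are therefore not identical.

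**Power.** Inputs: model (1), two predictors, two-sided test (section 4.1). Alpha is not in the visible text and Fig. 3 is not shown, so I assume 0.05. The test of one regression coefficient uses a noncentral t with δ = √(f2 × N) and df = N − 3.

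- The protocol's own figure first: N = 100, f2 = 0.075 gives δ = √7.5 = 2.739, df = 97, power 0.774. The protocol states 0.8. The gap is small, depends on the assumed alpha and does not bear on this point.
- The protocol's figure at n = 70 with f2 = 0.1: δ = √7.0 = 2.646, df = 67, **power 0.741**.

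| Loss | n analysed | Power at f2 = 0.1 |
|---|---|---|
| 0% | 100 | 0.879 |
| 10% | 90 | 0.843 |
| 20% | 80 | 0.798 |
| 30% | 70 | 0.741 |

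**Would ordinary imputation remove the bias?** Complete-case regression already conditions on treatment and WAZpre. Imputing WAZpost from WAZpre under missing-at-random adds no information about the lost children. It helps only if other Visit 1 variables predict both loss and WAZpost beyond WAZpre.

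A simulation illustrates this. It had 100 children with 15 of 50 lost per arm. Loss depended on the outcome residual in the intervention arm only, and the lost children were about 0.8 SD worse than completers. The expected bias is gap × share lost = 0.8 × 0.30 = 0.24 SD. The simulated bias was 0.247 SD for complete cases and 0.245 SD after within-arm imputation from baseline WAZ and one uninformative covariate. The 0.8 SD gap and the one-arm pattern are assumptions, not figures from the protocol. The lesson is the comparison between methods, not the size of the bias.

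**The case against.** The best defence is that the ITT sentence only says children are grouped by allocation, in contrast with the per-protocol set, and that the no-imputation sentence openly discloses how gaps are handled. On that reading there is an imprecise label, not a defect. Part of this stands: the sentences clash only for children who miss Visit 2, and the no-imputation rule is stated plainly. But the population sentence says that all randomised participants are included in the analyses, and the stated model cannot deliver that. Nor is this a detail left to an analysis plan, since the article itself fixes the rule.

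A reader might infer more than the document supports, in four ways:

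- *That the ITT safeguard is absent altogether.* It is not. Non-adherent children who attend Visit 2 are analysed as assigned, and the Discussion claims only that ITT deals with non-compliance and protocol deviations.
- *That 30% loss is expected.* It is a planning ceiling, raised in connection with per-protocol analyses.
- *That power falls to 0.62.* That figure pairs n = 70 with f2 = 0.075, which section 4.1 states for 100 participants. For n = 70 it names f2 = 0.1.
- *That bias could consume a fixed share of the planned effect.* With 1:1 allocation, f2 = 0.075 corresponds to 2 × √0.075 = 0.548 SD. That is the smallest effect the protocol says it can detect, not a planned effect, and the document gives no basis for the outcome gap between lost and retained children.

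It may also be tempting to fill gaps with routine weights. Section 3.7 mentions regular check-ups but promises no recorded weights, dates or methods.

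**Conclusion.** The point holds in a limited form. As written, the primary analysis is a complete-case analysis by assigned arm, and the statement that it includes all randomised children is wrong for anyone without a Visit 2 weight. What is missing is protection against loss of outcomes; protection against non-adherence remains.

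At the protocol's ceiling, 30 of 100 children would be absent and power for f2 = 0.1 would be about 0.74, assuming two-sided alpha 0.05. The size and direction of any bias cannot be derived from the document. It depends on whether loss is related to outcome beyond baseline WAZ and whether that relation differs between arms. Because the ITT and per-protocol comparison is blind to it, the plan has no means of showing how far the conclusion depends on the missing children.

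**What to change.** Make two changes to section 4 before the data are unblinded.

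1. State that the primary analysis uses children as assigned who have an observed WAZpost, and withdraw the claim that all randomised children are included. Say in section 4.1 that drop-out without a Visit 2 weight reduces the ITT regression as well as the per-protocol one.
2. Replace the blanket no-imputation rule with a pre-specified sensitivity analysis on all randomised children. Impute WAZpost by multiple imputation within arm from WAZpre, sex, GMFCS group, age, EDACS level and dietary intake, all of which are available at study entry. Then apply delta-adjusted (tipping-point) shifts to the imputed values, varied separately by arm, and report how large a shift would change the conclusion. The delta step is essential, because imputation under missing-at-random alone would not address outcome-dependent loss.

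The cost is a little more analysis work on data already planned, with no new visits, and a somewhat less favourable description of the ITT population. The change does not restore the power lost to drop-out.
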